#### Data analysis – overall considerations

We will present results as means and 95% confidence intervals. We will include *p*-values in our reports, but will aim not to present them in any external reports or papers given the widespread misunderstanding of their meaning [17]. We will use residual checks for all our models and will look for non-normality and outliers. These checks will be published as a supplementary to any paper and on *github* (https://github.com/[name]/LOCATE).

#### Per protocol definition

We will use an intention-to-treat approach meaning that participants will be analysed according to their randomised group, regardless of whether they followed that model of care [18]. In a sensitivity analysis we will use a per protocol analysis by only including patients that attended their Fibroscan appointment and had a successful scan. The per protocol analysis will be applied to the primary and secondary outcomes, and the economic analysis.

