### Aims

#### Primary clinical outcome

The time to diagnosis of high-risk NAFLD will be calculated based on the number of participants in each arm who receive a diagnosis of clinically significant fibrosis (transient elastography (TE) over 8.0 kPa) [7], with the time measured from date of GP referral to a confirmed diagnosis.

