#### Randomised to LOCATE

Study participants randomised to the new model of care will be invited to attend a local clinic to have their suspected NAFLD assessed with mobile transient elastography, using the Fibroscan machine. The invitation and assessment will be made by a specialist study nurse, who will write a report for the hepatologist. The hepatologist will triage patients to low- or high-risk, depending on the assessment of liver scarring and potentially other clinical indicators.

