#### Randomised to usual care (comparator)

For those participants randomised to usual care, their referral letters will be dealt with in the usual way, and the patients will wait to see a hepatologist at the hospital clinic as originally intended.

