#### Fibroscan service

The Fibroscan service will enable participants to undergo reliable assessment of the severity of liver fibrosis and to identify those with advanced fibrosis and cirrhosis who need both secondary care input and surveillance for liver cancer. The mobile Fibroscan clinics will occur on a rotational basis in the two regions using GP clinics and primary care facilities.

The Fibroscan will give the following test results:
Liver stiffness measurement - a marker of clinically significant fibrosis or advanced cirrhosis.Controlled attenuation parameter, to detect and quantify steatosis [12].

Examinations will be performed by a trained clinical nurse with extensive Fibroscan experience. Using an experienced operator is very important for producing reliable scans. Participants who did not attend an arranged appointment will be offered another appointment.

Around 7% of Fibroscans performed do not provide a valid reading. This is multifactorial, including issues such as skin to capsule depth, body habitus and rib spacing. These participants will be scheduled for a hepatology clinic visit as per the usual model of care. We will record the number of times the scan was unsuccessful and the reason why.

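### The per-protocol set is selected on the scan that the trial is timing, and its rule does not say how usual-care participants qualify

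*Protocol article*

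**What the plan says.** The section Per protocol definition makes intention-to-treat the main approach and then adds: "In a sensitivity analysis we will use a per protocol analysis". Membership is fixed as "only including patients that attended their Fibroscan appointment and had a successful scan". The scope is wide: "The per protocol analysis will be applied to the primary and secondary outcomes, and the economic analysis". The section Planned subgroup and adjusted analysis lists the analysis again.

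Four other parts of the protocol bear on this rule:

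- **Secondary clinical outcomes** include the time to a first successful Fibroscan. Analyses of secondary outcomes assigns it Kaplan–Meier plots and a Weibull model.
- **Primary clinical outcome** requires an elastography reading above 8.0 kPa, "with the time measured from date of GP referral to a confirmed diagnosis".
- **Randomised to LOCATE**: participants "will be invited to attend a local clinic to have their suspected NAFLD assessed with mobile transient elastography".
- **Randomised to usual care**: no Fibroscan appointment is described; "the patients will wait to see a hepatologist at the hospital clinic as originally intended".

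The section Fibroscan service adds: "Around 7% of Fibroscans performed do not provide a valid reading". It attributes failures partly to body habitus and sends those participants to the hepatology clinic under the usual model.

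**The concern.** Membership of the set depends on something that happens after randomisation and that the intervention is designed to change. For time to first successful Fibroscan, the membership event and the endpoint are the same. Any arm that is filtered therefore contains only participants with the event, and those not scanned by the end of follow-up are deleted when they should be censored. The primary event also cannot occur without a reading.

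The rule does not say how a usual-care participant qualifies. Two readings are open:

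- **Both arms filtered.** Usual-care participants still unscanned at 12 months are removed. Their delay is what the trial sets out to measure, so the scan-time comparison moves towards no difference.
- **LOCATE filtered, usual care kept whole.** Non-attenders and failed scans leave one arm only, so the comparison moves in favour of LOCATE.

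A per-protocol result is commonly read beside intention-to-treat as a check on it. Here it could seem to contradict a correct main result, or seem to confirm a benefit that is not there. Which of these happens would turn on an unstated choice, in a trial that is open-label.

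**Working it through.** The protocol gives no figure for the size or effect of this set, so there is none to reproduce. The check below is for time to first scan only.

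**Inputs from the protocol.** Means of 180 days (usual care) and 90 days (LOCATE), from Sample size and statistical power; 1:1 allocation of 234, so 117 per arm; one year of follow-up, taken as 365 days; about 7% invalid scans.

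**Assumptions.** The protocol's means are for time to diagnosis of high-risk disease and are borrowed here for scan waits. Waits are exponential unless stated. Everyone attends. Where failed scans are included, 7% applies in both arms.

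**Step 1: who is removed.** The proportion unscanned at 365 days is q = exp(−365/m).
- Usual care, m = 180: q = 0.132, and 117 × 0.132 ≈ 15 participants.
- LOCATE, m = 90: q = 0.017, and 117 × 0.017 ≈ 2 participants.

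**Step 2: mean wait among those kept.** This is m − 365q/(1 − q).
- Usual care: 180 − 365 × 0.1316/0.8684 = 124.7 days.
- LOCATE: 90 − 365 × 0.0173/0.9827 = 83.6 days.

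**Step 3: time ratios without failed scans.** With proper censoring an exponential fit recovers 180 and 90 days, ratio 0.50.
- Both arms filtered: 83.6/124.7 = 0.67.
- LOCATE only filtered: 83.6/180 = 0.46.
- LOCATE only filtered, no true effect (180 v 180): 124.7/180 = 0.69.

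Large-sample simulation with the planned Weibull model gives about 0.67, 0.47 and 0.70. With no true effect, filtering both arms leaves the ratio at 1.00, so that reading dilutes an effect but does not create one.

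**Step 4: 7% failed scans, exponential fit (follow-up time divided by events).**
- Usual care, all kept: (0.93 × 180 × 0.8684 + 0.07 × 365)/(0.93 × 0.8684) = 170.9/0.808 = 211.6 days.
- LOCATE, all kept: (0.93 × 90 × 0.9827 + 0.07 × 365)/(0.93 × 0.9827) = 107.8/0.914 = 118.0 days.
- Intention-to-treat ratio: 118.0/211.6 = 0.56 (Weibull fit 0.54).
- LOCATE only filtered: 83.6/211.6 = 0.395 (Weibull fit 0.39 to 0.40).

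**Step 5: sensitivity to the assumed waits (Weibull simulation, 180 v 90 days unless stated).**

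| Scenario | Intention-to-treat | Both arms filtered | LOCATE only filtered |
|---|---|---|---|
| Shape 1, no failures | 0.50 | 0.67 | 0.47 |
| Shape 1.5, no failures | 0.50 | 0.59 | 0.50 |
| Shape 3, no failures | 0.50 | 0.50 | 0.50 |
| Shape 1, 7% failures | 0.54 | 0.68 | 0.39–0.40 |
| Shape 1.5, 7% failures | 0.56 | 0.59 | 0.44 |
| No true effect (180 v 180), shape 1, 7% failures | 0.99 | 1.00 | 0.60 |
| No true effect (180 v 180), shape 1.5, 7% failures | 1.00 | 1.00 | 0.75 |

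Longer assumed usual-care means (270 and 365 days, not in the protocol), with the LOCATE mean still half, raise the both-arms ratio to about 0.77 and 0.83 under exponential waits.

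**The case against.** The strongest reply is that the analysis is labelled a sensitivity analysis, that intention-to-treat carries the conclusions, and that every per-protocol analysis gives up some protection from randomisation. The first two points stand and limit the consequence. The third does not meet the specific problem, which is a set selected on the endpoint it is then used to analyse.

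A reader might infer that the rule deletes the usual-care patients who waited longest and so pulls results towards no difference. The text does not support that as the only outcome. Fibroscan appointments are described only in the LOCATE pathway, so the rule may well be meant for that arm alone. On that reading no usual-care participant is removed and the bias runs the other way.

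The size is also open to challenge, and these points stand:

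- The protocol gives no distribution of scan waits. Its only spread figure, a standard deviation of 10 days in the sample size section, is unclear in meaning. If waits were that tight around 180 days, none would pass 365 days and the both-arms bias would vanish.
- The primary outcome is timed from GP referral, while the chart audit is 12 months after recruitment. If scan time also starts at referral, an assumed gap of 60 to 90 days cuts usual-care removals from 13% to between 8% and 10%, and the both-arms ratio to between 0.62 and 0.64.

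A reader might also conclude that an instrumental-variable analysis is required. It is one option with its own assumptions. For time to first scan it is circular, because treatment received would be the event itself.

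**Conclusion.** The point holds in this form. The per-protocol set is selected on the endpoint of one secondary outcome and on a precondition of the primary event, and its rule is undefined for one arm. Either reading can distort the scan-time comparison, in opposite directions.

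Under exponential waits the both-arms reading turns 0.50 into about 0.67. The LOCATE-only reading gives about 0.47, or 0.39 to 0.40 with failed scans against 0.54 by intention-to-treat, and it can produce an apparent benefit where there is none. These sizes rest on an assumed wait distribution. Without failed scans the bias is negligible at Weibull shape 3 under either reading.

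Two stronger conclusions are not supported. The main intention-to-treat results are not affected. Nor is there a calculated bias for the primary outcome or the costs: the selection applies to them too, but its size there is not quantified.

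**What to change.** Amend the per-protocol section as follows:

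1. Do not apply the scanned-only set to time to first successful Fibroscan or to the primary outcome. Keep unscanned participants in their randomised arm, censored at the end of follow-up.
2. For the other outcomes and the economic analysis, state what counts as adherence in each arm, including how a usual-care participant qualifies.
3. Report the proportions who attended and who had a valid scan beside the intention-to-treat results.

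A complier-average analysis with randomised arm as the instrument could be added for outcomes other than scan time, with its exclusion restriction stated. It is optional, and its intervals would be wider than those from a simple subset.

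The three changes need wording only and no new data. The price is that the per-protocol analysis covers fewer outcomes.

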#### Analysis of the primary outcome

We will use survival analysis methods to examine the primary outcome of time to diagnosis of high-risk NAFLD. We will use Kaplan–Meier plots to highlight any differences between the usual care and intervention groups. We will use parametric Weibull survival models to examine a statistical difference. We will check the parametric assumption and the model residuals.

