### Statistical analysis

#### Sample size and statistical power

We have a minimum total sample size of 156 participants for our primary outcome of time to diagnosis, but we will aim for a sample size of 234. Two hundred and 34 participants will give us a 95% power to detect a 50% reduction in the primary outcome of time to diagnosis of high-risk disease. Our lower sample size of 156 gives us an 83% power. We used a two-sided 5% significance level. We assumed an average diagnosis time of 180 days in the usual care group, and a halving of this time in the intervention group. We assumed that 5% of participants would be censored due to death or loss to follow-up. The sample size was estimated by simulating survival data using the “sim.survdata” function from the “coxed” package in *R* using 1000 simulations [16]. We assumed a log-normal hazard function with a standard deviation of 10 days. The statistical code to run the sample size is available here: https://github.com/[name]/LOCATE. We assume that half of all patients approached will agree to participate, hence, we aim to approach 468 people.

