#### Analyses of secondary outcomes

For the three time-to-event outcomes of NAFLD-associated admissions and re-presentations, and first fibrosis assessment, we will use Kaplan–Meier plots and Weibull survival models as per the primary outcome.

For health-related quality of life we will model the participants’ 12-month result whilst adjusting for their baseline, which is the equivalent to examining the within-participant change in quality of life and helps adjust for regression to the mean [19, 20]. We will use a linear regression model and check the model residuals.

Statin use will be compared between groups by examining the number of participants given a new statin script during the follow-up period. The denominator will be the number of patients not on statins at the time of their referral letter to the hepatology clinic. We will compare the numbers using a 2-by-2 table and Chi-squared test. Deaths and HCC detection will be compared between groups using a 2-by-2 table. As these two outcomes are likely to be rare, we anticipate needing to use Fisher’s exact test to look for statistical differences between the two groups.

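### Under the protocol's own log-normal planning inputs, the Weibull primary test has a type I error of about 12–13% rather than 5%; this is no forecast for the trial, but a stratified log-rank/Cox analysis avoids the exposure cheaply

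*Protocol article*

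**What the plan says.** Two sections of the protocol article describe the distribution of the primary outcome, time to diagnosis of high-risk NAFLD.

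- *Sample size and statistical power*: "We assumed a log-normal hazard function with a standard deviation of 10 days"; "We assumed that 5% of participants would be censored due to death or loss to follow-up"; "We used a two-sided 5% significance level"; and "We assumed an average diagnosis time of 180 days in the usual care group, and a halving of this time in the intervention group". The stated power is 95% with 234 participants and 83% with 156.
- *Analysis of the primary outcome*: "We will use parametric Weibull survival models to examine a statistical difference. We will check the parametric assumption and the model residuals". Kaplan–Meier plots are planned as a display. No log-rank test, Cox model or robust standard error is mentioned.

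*Analyses of secondary outcomes* carries the method over to NAFLD-associated admissions, re-presentations and first fibrosis assessment: "Weibull survival models as per the primary outcome".

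*Data analysis – overall considerations* says results will be shown with 95% confidence intervals and that p-values will preferably be left out of papers. *Randomisation* stratifies by health service.

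**The concern.** A log-normal hazard rises and then falls. A Weibull hazard can only rise, fall or stay flat. The distribution used to size the trial is therefore one that the primary model cannot fit.

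This affects more than fit. When a Weibull model is fitted to log-normal times with few censored, its model-based standard error for the treatment effect is too small, so the test rejects too often under the null and the intervals are too short. Leaving p-values out of papers does not help, because the published intervals rest on the same standard error.

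The promised check has no stated consequence. Either the Weibull result stands despite misfit, or the primary model is chosen after the data are seen, in an open-label trial.

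**Working it through.** **Inputs.** All are from the sample size section unless noted: log-normal times (my reading of the stated log-normal hazard function), SD 10 days, means of 180 and 90 days, 5% censored, two-sided 5%, N = 234 or 156, 1:1 allocation, one year of follow-up (*Study design*). An SD of 10 days at a mean of 180 is a log-scale SD of √ln(1 + (10/180)²) = 0.055.

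**The stated power.** It does not reproduce from these inputs.

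- With the literal SD of 10 days, simulated power is 100% at both sample sizes.
- With a hazard ratio of 0.5, events = 0.95N and power = Φ(√(events/4) × ln 2 − 1.96). For N = 234: events 222.3, Φ(5.17 − 1.96) = 99.9%. For N = 156: events 148.2, Φ(4.22 − 1.96) = 98.8%.
- A log-scale SD near 1.3, which is not stated, comes close: log-rank power 94.9% and 84.1%.

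That is a separate problem. It does not affect the type I error below, which hardly depends on the spread when few are censored.

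**Large-sample type I error, no censoring.** Let log T be normal with SD s, and fit a Weibull model with shape k. Put w = k(log T − location), which is normal with variance v = (ks)².

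1. The fitted values solve E[e^w] = 1 and E[w e^w] − E[w] = 1. The first gives E[w] = −v/2. Then E[w e^w] = v/2, so the second gives v = 1, that is k = 1/s.
2. The treatment score per participant is proportional to e^w − 1. Its true variance is e^v − 1 = e − 1 = 1.718. The model takes it to be 1.
3. The true standard error is √1.718 = 1.311 times the model-based one, whatever s is.
4. Actual level = 2 × (1 − Φ(1.96/1.311)) = 2 × (1 − Φ(1.495)) = 13.5%. A nominal 95% interval then covers about 100 − 13.5 = 86.5%.

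**Simulated type I error, 5% censored.** There were 10,000 or more null trials per case, so the Monte Carlo standard error near 13% is √(0.13 × 0.87/10,000) = 0.3 points.

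| Setting | Weibull | Log-rank |
|---|---|---|
| SD 10 days, N = 156, 5% censored at random | 12.4–12.9% | 5.3% |
| SD 10 days, N = 234, 5% censored at random | 12.2–12.5% | 5.2% |
| SD 10 days, 365-day cut-off added | 12.7–13.3% | – |
| Log-SD 0.5–2.0, N = 156 | 12.3–13.0% | 4.9–5.6% (both N) |
| Log-SD 0.5–2.0, N = 234 | 12.4–13.4% | as above |

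The first two rows cover the likelihood-ratio test and two Wald tests. The Cox Wald test at SD 10 days gave 4.8% (N = 156) and 5.0% (N = 234). A further set of runs under the planning inputs gave 12–15% for Weibull and 4–6% for log-rank. At SD 10 days the cut-off changes nothing, because times around 180 days do not reach day 365. With exponential times, where the Weibull model is correct, its error was 4.8%.

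**Where the inflation shrinks.**

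- 365-day cut-off with log-SD 0.5–2.0: Weibull 5.4–7.9%.
- Only some participants able to have the event (assumed shares): about 2–6% if 15%, 4–6.5% if 30%, 5–8% if 50%. A separate run over shares of 17–40% gave 4.4–5.6%.

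**Power, log-rank against Weibull.** At log-SD 1.3 with 5% censored: 94.9% v 94.2% (N = 234) and 84.1% v 85.3% (N = 156). At wider spreads the Weibull test rejects more often, for example 78.0% v 80.9% at log-SD 1.4 and N = 156. Its null rejection rate there is about 12%, so this is not a like-for-like gain. At the literal SD of 10 days both tests have 100% power and the comparison says nothing.

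**The case against.** **The 13% does not describe this trial.** A reader might infer that the trial will run with a 13% false-positive rate. The documents do not support that. *Primary clinical outcome* counts only participants with transient elastography over 8.0 kPa, and *Background* says 60 to 90% of NAFLD patients lack advanced fibrosis. Low-risk participants cannot supply the event. With few able to have it, the Weibull test is near nominal. This objection stands and limits the point to the planning assumptions.

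**A simulation device is not a forecast.** Generating data under one model and analysing under another is common and not an error in itself. That is fair. What remains is that, for the pair stated here, the 5% level is not delivered.

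**The promised check would catch the misfit.** In null log-normal trials (1,000 per case, 5% censored, log-SD 0.5 and 1.0), AIC preferred log-normal over Weibull in 99.1–99.2% at N = 156 and 99.8–99.9% at N = 234. Taking the better-fitting model gave 4.2–7.0% (Monte Carlo standard error about 0.7 points), against 10.8–13.6% for Weibull throughout. So the 12–13% requires keeping the Weibull result despite a failed check. This stands too, but the article names neither the criterion nor the replacement model.

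**A fallback rule may sit in an analysis plan not shown.** Agreed, and its absence alone is not the point. The point is the stated choice of test, for which a method that does not depend on the distributional form is available at little cost.

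**Secondary outcomes.** A reader might infer the same inflation for all of them. For first fibrosis assessment it arises only if most participants in both arms are scanned within the year. The article does not say so, and it describes long waits under usual care. Nothing was computed for admissions or re-presentations.

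**Conclusion.** The point holds in a limited form. Given log-normal times, about 95% of participants reaching the event and the Weibull result being kept, the nominal 5% primary test has a type I error of about 12–13% at either sample size, and its model-based intervals are too narrow. Log-rank and Cox tests stay at about 5%.

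The result depends on how many participants have the event. It falls to about 5–8% with a one-year cut-off and log-scale SD of 0.5–2.0, and to about 2–6.5% if 15–40% can be diagnosed with high-risk disease. Those spreads and shares are assumptions; the article does not give them.

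This is a worthwhile, cheap improvement in method. It does not show that the primary result will be invalid.

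**What to change.** In *Analysis of the primary outcome*, pre-specify a log-rank test and a Cox model, both stratified by health service (the randomisation stratum), as the primary time-to-event analysis. Keep the Weibull model as supportive. This fits the Kaplan–Meier plots already planned and removes any choice of primary model after the data are seen. Apply the same wording to the time-to-event secondary outcomes.

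A minimal alternative is to keep the Weibull model as primary with a robust variance, stated in advance. A difference in restricted mean time would be an optional addition; this point does not require it.

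The cost is one paragraph of analysis wording and a few lines of R, with a small loss of efficiency if times really are Weibull.
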